## Abstract

The global aging trend increases chronic diseases and lowers quality of life. Exercise is vital for physiological, cognitive, and mental health, countering age-related decline. Outdoor multidomain interventions enhance adherence, motivation, and resilience, supporting independence and well-being. **Objectives**: This paper aimed to apply an outdoor exercise protocol for middle-aged and older people and to study its preliminary effects on cognitive state, body composition, cardiovascular health, physical fitness, physiological function, physical activity, frailty, incidence of sarcopenia, and satisfaction with life. **Methods**: This protocol describes an eighteen-week, two-pronged, parallel, single-blind randomized controlled trial. This paper complies with the Consort and SPIRIT guidelines. A cohort comprising a minimum of fifty-two older adults from the University for Seniors program will be equally allocated to a multidomain training group (TG) and a passive control group (CG). **Intervention**: The TG will follow a multidomain outdoor intervention twice a week for a complete duration of 18 weeks, with recommendations for additional autonomous cardiorespiratory training. The supervised sessions will be divided into a 10-min warm-up session focusing on activation and joint mobility, followed by 40 min of resistance training, cardiorespiratory training, and balance and coordination; and it concludes with a 10-min cool-down featuring flexibility, relaxation, and playful emotional intelligence tasks. Cognitive training will be integrated across different parts of the session. **Conclusions**: This preliminary study aims to explore the feasibility and potential effectiveness of outdoor multidomain training in improving the health of older adults. Importantly, by including late middle-aged adults from the age of 55, this study also aims to explore the potential of preventive strategies initiated before reaching old age. This reflects a broader conceptualization of healthy aging as a lifelong process, where early interventions may help mitigate decline and extend independence into later life. The partnership between health professionals and physical activity fosters independence for older adults, addressing the increasing burden on health services.

## 1. Introduction

The rise in life expectancy, driven by advancements in healthcare systems and other factors, has contributed to a substantial increase in the population of older adults [1,2,3]. This demographic shift brings with it a host of challenges related to physical and cognitive health [4]. As people age, they become more vulnerable to frailty, disability, and chronic diseases, leading to a decline in overall quality of life [5]. Furthermore, one of the most concerning aspects of aging is cognitive decline, which can significantly impact independence and well-being [4]. Depression also rises among middle-aged and older adults, representing a public health issue linked to emotional distress, increased risk of dementia, and higher risk of death from other causes [6,7]. This highlights the urgent need for effective interventions to prevent or delay its onset [8,9].

Although the World Health Organization (WHO) and the United Nations define older adults as individuals aged 60 years and above [2,3], emerging evidence suggests that initiating preventive interventions from late middle age—starting around 55 years old—can significantly enhance long-term health outcomes and support healthier aging trajectories [10]. This upstream approach aims to mitigate age-related decline before its onset, fostering resilience and prolonged independence. Moreover, middle-aged individuals with chronic diseases are more likely to experience a pronounced deterioration toward frailty later in life, so starting preventive work as early as possible seems like an excellent strategy to slow the effects of aging [11].

Against this background, previous research has demonstrated the positive effects of systematic physical exercise on functionality, quality of life, independence, cognitive status, and physical and psychological health in late middle-aged adults and older adults [12,13,14,15]. More specifically, cardiorespiratory exercise, such as walking or cycling, has been linked to improvements in cardiovascular fitness and cognitive function, including memory and attention [12]; while strength training, based on lifting weights or using resistance bands, can help maintain muscle mass and strength, reducing the risk of falls and frailty [13,14]. Despite these benefits, physical activity levels in the older population are exceptionally low, as evidenced by only 33% and 17% of the population aged over 65 meeting recommended cardiorespiratory and strength training thresholds by the WHO, respectively [16].

In addition to the benefits of physical exercise, cognitive training has gained attention as a potential strategy for preserving cognitive function in middle-aged and older adults [15,17,18]. Cognitive training programs typically involve exercises designed to challenge memory, attention, and problem-solving skills [19]. While the evidence for the effectiveness of cognitive training alone is mixed [20], research suggests that multidomain interventions may have synergistic effects, resulting in greater improvements compared to single-component interventions [21]. Dual-task training, combining physical exercise with cognitive tasks, may enhance cognitive flexibility by engaging executive functions, especially when the physical component is either automated or taxing enough to recruit prefrontal resources [22]. These principles are supported by recent systematic reviews and meta-analyses highlighting the superior effects of multidomain interventions over single-modality approaches [23,24]. This selection of components is grounded on the theoretical framework of “multidomain synergy”, which proposes that simultaneously targeting multiple physiological and cognitive systems produces cumulative and interactive benefits [21]. Specifically, the combination of resistance, cardiorespiratory, balance, and cognitive training is designed to enhance neuroplasticity, functional capacity, and psychosocial well-being through mechanisms such as muscle–brain crosstalk, dual-task challenge, and enriched environments [25,26,27,28].

Multidomain interventions that integrate physical and cognitive exercise have emerged as a promising approach to promoting healthy aging, reducing the risk of cognitive decline and mitigating the effects of neurodegenerative diseases [29,30,31]; improving cognitive function [17]; and improving functionality, quality of life and overall health of the older people [31,32,33,34,35,36]. Not surprisingly, previous studies have demonstrated the benefits of a two-year multidomain program in individuals aged 60–77 years old with dementia and cognitive impairment, finding an improvement or maintenance of cognitive functioning [21]. Similarly, a one-year multidomain program in individuals with pre-frailty or frailty has been shown to reduce depression, while enhancing physical, functional, and cognitive performance, thereby supporting its effectiveness in supporting healthy aging [37]. In addition, the potential benefits of multidomain exercise in mitigating physical and cognitive decline, as well as depression, have gained relevance during the COVID-19 pandemic [38,39].

These types of interventions may also hold significant potential for middle-aged adults under the age of 60, as aging is a gradual and multifaceted process that benefits from early engagement in multidomain training to promote healthy aging. Preventive strategies implemented before old age, particularly those addressing both physical and cognitive health, can foster resilience and delay age-related decline. Recent evidence has highlighted the effectiveness of these interventions even in non-older populations, supporting their role in healthy aging from an earlier stage of life [18].

It is worth noting that previous research with multi-domain interventions both in middle and older adults has mostly been carried out in indoor environments, such as fitness centers. Nonetheless, outdoor settings may offer added psychological and engagement benefits [21,29]. More specifically, outdoor exercise settings, such as purpose-built seniors’ parks or outdoor gyms, have shown promising outcomes in supporting physical health and mental well-being in older adults, beyond traditional walking-based activity. Despite logistical challenges, these environments have been found to enhance accessibility, enjoyment, and long-term engagement, suggesting that well-designed open-air spaces may serve as viable platforms for implementing multidomain programs in community settings [31].

However, there are no previous studies that have analyzed the effects of a multidomain program on healthy middle-aged and older adults with interventions of less than one year, which could help make implementation more feasible and reduce drop-out rates [25]. Furthermore, no previous research has examined the effects of a multidomain intervention conducted outdoors, even though outdoor exercise interventions are expected to become pivotal in interventions to improve the health of older people [26].

Consequently, the aim of this protocol is to conduct a preliminary study that explores the effects of an 18-week, twice-weekly outdoor multidomain intervention—including physical exercise, cognitive stimulation, and social engagement—on the health of late middle-aged and older adults. This study also seeks to assess the feasibility and acceptability of the intervention, thereby informing the design of future large-scale trials by evaluating both its potential effects and feasibility. Additionally, this study aims to assess the feasibility and acceptability of the ACTIVA intervention among older adults, to inform future larger-scale trials. We hypothesize that the ACTIVA-Senior program, conducted entirely in an open-air environment, will lead to significant improvements in cognitive, physical, and psychological outcomes. Moreover, the outdoor setting may contribute to greater adherence, enhanced social interaction, and a more enjoyable and relaxed experience, potentially amplifying the overall impact of the intervention on the participants.

This protocol describes a single-blind randomized controlled trial designed as a preliminary and exploratory study. Its dual aim is to evaluate the feasibility and acceptability of an outdoor multidomain intervention for late middle-aged and older adults and to examine its initial effects on cognitive, physical, and psychological health outcomes.

## 2. Materials and Methods

### 2.1. Design

This study intends to run an 18-week, two-pronged, parallel, single-blind randomized controlled trial (RCT; ClinicalTrial.gov NCT05481346: https://beta.clinicaltrials.gov/study/NCT05481346 (accessed on 2 August 2022)). It follows the guidelines outlined in the Consolidated Standards for Reporting Trials (CONSORT) recommendations on RCTs [40]. In addition, it adheres to the Standard Protocol Items: Recommendations for Interventional Trials (SPIRIT);both checklist are available in the Supplementary Materials. The research will take place in the sports facilities of the University of Almeria, Spain, and the evaluations will be conducted at the university’s sports science laboratory. Participants have already been selected and are awaiting the commencement of the trial. Prior to the start of the program, participants will be assessed for the pre-test, and then they will proceed to a 2-week familiarization program.

To ensure participant safety during the outdoor training, a comprehensive plan will be implemented, with all instructors trained in basic first aid and emergency response protocols. In case of injury or medical emergency, participants will be referred to medical professionals, and emergency contacts will be available. Weather-related challenges will be managed with real-time weather monitoring; sessions will be rescheduled if adverse conditions (e.g., extreme heat, rain, or storms) are predicted. Participants will be informed of weather conditions and provided with guidelines on appropriate attire.

In accordance with SPIRIT Item 13, Table 1 presents the schedule of enrolment, interventions, and assessments.

### 2.2. Ethical Considerations

Throughout the expected research, the ethical principles for studies involving human subjects, as proposed in the Declaration of Helsinki and its subsequent revisions, will be strictly adhered to. Approval from the Ethics Committee of the University of Almeria was sought (register code: UALBIO2022/011). All the future participants have now received verbal and written information about the research protocols, including an informed consent document outlining the study’s procedures, objectives, risks, benefits, and confidentiality measures. Participants will be able to withdraw at any time without explanation, and a coding system will ensure confidentiality. Only research team members will access participant data, and each participant will receive a final report with their results at the study’s conclusion.

### 2.3. Sample Size and Power Calculation

The sample size was calculated using RStudio 3.15.0 software (RStudio Inc., Boston, MA, USA) prior to the recruitment of participants. Assuming a study design with a 5% Type I error rate and 75% statistical power, the calculation was informed by effect sizes reported in similar multidomain interventions. These effect sizes were drawn from studies targeting physical, cognitive, and psycho-physiological outcomes in older adults [41,42,43]. A potential 15% dropout rate has been accounted for in the final estimate [44]. This yielded a total sample size of 52 participants (26 per group). While this sample size is considered sufficient to detect meaningful changes, the relatively small cohort may increase the risk of Type II errors. Therefore, upon completion of the trial, the results will have to be interpreted with caution and regarded as preliminary until validated by studies with larger samples.

### 2.4. Participant Recruitment

Although baseline assessments and the intervention have not yet commenced, participant recruitment and randomization have already been completed. A convenience sampling method was employed to recruit middle-aged and older adults through direct communication and email outreach within the senior university program at the University of Almeria. All potential participants were contacted individually.

To be included in the study, participants were expected to meet the following criteria: (a) aged 55 or over; (b) being physically independent; (c) being enrolled in the university for seniors’ program; and (d) passing a medical examination prior to participation, including an electrocardiogram (EKG) under stress conditions. The exclusion criteria were: (a) engaging in moderate or vigorous cardiovascular exercise systematically (≥150 min per week); (b) performing strength training systematically in the last 2 months; (c) having a body mass index (BMI) greater than 35 kg/m^2^; (d) diagnosed with ischemic heart disease, severe aortic stenosis, uncontrolled arrhythmias, decompensated heart failure, acute myocarditis, severe peripheral arterial disease, cerebrovascular accident, thromboembolic disease, aortic aneurysm, clinically significant renal or hepatic failure, severe chronic obstructive pulmonary disease (COPD), clinically significant acute infections, severe psychiatric illness, uncontrolled metabolic diseases, musculoskeletal pathologies, or osteoporosis; (e) uncontrolled blood pressure (systolic blood pressure > 180 mmHg and diastolic blood pressure > 110 mmHg); (f) other pathologies contraindicating physical exercise, identified through the mandatory medical examination that all participants underwent; (g) participants not attending both of the assessments; and (h) participants of the TG who do not attend at least 75% of the sessions (Figure 1).

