The cardiorespiratory component of the intervention will involve two sets of four-minute bouts of continuous aerobic activity, with a 40-second rest between sets. The participants will be instructed to begin at a moderate intensity and gradually increase to a vigorous pace, guided by their ability to speak comfortably during exercise (i.e., the talk test) [48]. Exercise intensity will be further monitored using the Borg Rating of Perceived Exertion Scale, aiming for a perceived effort of 6–7 out of 10 [49].

Flexibility training will be based on passive static exercises in the cool-down period. Exercises will consist of eight stretching exercises of one or two sets of 10 to 30 s per each one, with 15 s of rest between sets and exercises. The relaxation block will consist of different breathing exercises, body–mind movements (Tai Chi, Pilates, etc.), which will integrate breathing. With respect to the emotional intelligence task, this block will consist of different games involving collaborative tasks, expression of feelings, etc.

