## Figures and Tables

**Figure 1 healthcare-13-01110-f001:**
[figure not shown]
Consolidated Standards of Reporting Trials flow diagram showing the flow of participants through each stage of the study. NOTE: The follow-up accounts for potential participant exclusion based on expected attrition observed in previous studies.

**Table 1 healthcare-13-01110-t001:** SPIRIT schedule of enrolment, interventions, and assessments.

Study Period	Enrolment	Pre-Intervention (Pre-Test)	Familiarization (2 Weeks)	Intervention (Weeks 1–18)	Post-Intervention (Post-Test)	3-Month Follow-Up (Re-Test 1)	6-Month Follow-Up (Re-Test 2)
Informed Consent	X						
Eligibility Screening	X						
Randomization	X						
Baseline Assessments		X					
Multidomain Intervention			X	X			
Outcome Assessments					X	X	X

**Table 2 healthcare-13-01110-t002:** Distribution of content between the weekly sessions.

Session Part	Content	Details	Monitoring	Cognitive Integration
Warm-up (10 min)	- Activation exercises - Joint mobility	Playful tasks and movement prep activities; progressive cardiorespiratory stimulus.	RPE (Borg), trainer supervision	Sensorimotor activities, coordination-based games
Main (40 min)	First weekly session Local muscle endurance (1) Balance and coordination	Circuit of 8 exercises (6 strength, 2 balance/coordination). 3–4 sets of 10–12 reps. 20–30 s rest between exercises. Equipment: dumbbells, bands, TRX.	OMNI-RES RPE (6–7/10), trainer diary	Dual tasks (e.g., movement + verbal/cognitive tasks)
	Second weekly session Power training + local muscle endurance (2) Cardiorespiratory	Power block: 3 exercises, 2 sets of 6–8 reps. Load moved as fast as possible. Local muscle endurance block: 3 exercises, 3 sets of 10–12 reps. Cardio: 2 × 4 min intervals, moderate to vigorous using the talk test.	OMNI-RES RPE, Borg scale, trainer diary	Dual tasks, attention/memory components
Cool-down (10 min)	- Flexibility - Relaxation - Emotional intelligence tasks	Static stretching (8 exercises, 10–30 s), body–mind exercises (Tai Chi, breathing), emotional intelligence games (collaboration, expression of feelings).	Trainer checklist	Breathing visualization, reflective and emotional tasks
Autonomous training	Brisk walking (2×/week)	30+ min per session, moderate intensity. Monitored via self-reported training diaries and talk test.	Training diary (duration, distance, RPE)	—

**Table 3 healthcare-13-01110-t003:** Description of outcome measures.

	Dimension	Test	Description

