		Timed Up and Go test (TUG) + Gait speed test (4 m walk test—4MWT) + Short Physical Performance Battery (SPPB)	The severity of sarcopenia (functional performance) will be assessed using TUG, gait speed, and the SPPB test, following the indications of the European consensus on definition and diagnosis [6]. The tests will be performed according to the protocol of previous research [7]. Photovoltaic cells from Microgate (Bolzano, Italy) will be used for TUG and 4MWT. The SPPB battery includes the balance test, gait speed test, and chair stand test. The Total SPPB score, ranging from 0 to 12, will be calculated by adding the scores from the three individual tests, following previous studies [8].
	Cardiovascular state	Blood pressure and resting heart rate	Blood pressure and resting heart rate will be measured using a calibrated and automated device (Omron M6W, Omron Healthcare Ltd. Hoffman Estates, IL, USA), following the protocol of previous studies [9]
	Physical fitness	Upper and lower limbs muscle strength	Upper and lower limb isometric muscle strength will be evaluated using the functional electromechanical dynamometer Dinasystem. For this purpose, the following exercises will be performed randomly, maintaining the isometric phase for 6 s during evaluation: bilateral rowing; bilateral push from the seated position with shoulder abduction at 45° and elbow flexion at 90°; and the sit-to-stand test. All of this will follow the methodology of previous research [10].
		Velocity	The 10 m walk test (10MWT) will be used for the assessment of velocity. Photovoltaic cells from Microgate (Bolzano, Italy) will be used for evaluation. This test will be conducted following the guidelines of previous research [11].
		Cardiorespiratory fitness	The 6-minute walk test will be used for the assessment of cardiorespiratory fitness. The distance covered, heart rate at the end, and heart rate recovery at 1 and 3 min will be recorded, following previous studies [12].
		Flexibility	Sit-and-reach test with a box (Acuflex, Psymtec, Madrid, Spain) and back scratch test will be used for the assessment of flexibility, following the protocol of previous studies [13]
Secondary evaluations	Physical activity (PA)	International Physical Activity Questionnaire (IPAQ-SF)	The short version of the IPAQ-SF for adults will be used to analyze levels of PA [14]

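### Exclusion (e) is labelled uncontrolled blood pressure but joins its two limits with 'and', so a participant above only one limit does not meet it as written

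*Protocol article*

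**What the plan says.** Section 2.4 of the protocol article gives exclusion (e) as "uncontrolled blood pressure (systolic blood pressure > 180 mmHg and diastolic blood pressure > 110 mmHg". The words before the parenthesis name a condition. The parenthesis defines it by two limits joined with 'and'.

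Two other entry conditions in the same section bear on the point. Inclusion (d) requires "passing a medical examination prior to participation, including an electrocardiogram (EKG) under stress conditions". Exclusion (f) covers "other pathologies contraindicating physical exercise, identified through the mandatory medical examination that all participants underwent". Neither contains a blood-pressure figure.

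On training, Section 2.6 says of the cardiorespiratory block that participants will "begin at a moderate intensity and gradually increase to a vigorous pace", and Table 2 agrees: "Cardio: 2 × 4 min intervals, moderate to vigorous using the talk test". On measurement, Table 3 says "Blood pressure and resting heart rate will be measured using a calibrated and automated device" and lists this among the primary evaluations.

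On timing, Section 2.4 says that "participant recruitment and randomization have already been completed", while baseline assessments and the intervention have not started.

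**The concern.** The label and the definition of exclusion (e) do not describe the same group. The label reads as though it covers anyone whose blood pressure is out of control. The definition covers only those above both limits at once. A reader who goes by the label and a reader who goes by the definition would classify the same person differently whenever exactly one limit is exceeded.

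This matters because the criterion is a safety limit at entry. Those allocated to training do loaded power work and aerobic bouts that rise to vigorous pace, and both groups do isometric strength tests. If the printed definition is not the intended one, someone the sponsor meant to keep out may have been randomised. If it is the intended one, the label misleads anyone who applies or repeats the protocol. In both cases the document does not settle which rule was used.

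**Working it through.** The document gives no count or distribution of blood pressure, so there is no figure of the plan's to reproduce. The check is a truth table, followed by a search for any other passage that would close the gap.

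**Inputs.** From Section 2.4, exclusion (e): systolic limit 180 mmHg, diastolic limit 110 mmHg, connective 'and'. The four readings below are assumed, one for each possible combination.

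| Reading (mmHg) | Systolic > 180 | Diastolic > 110 | Excluded if 'and' (as printed) | Excluded if 'or' |
|---|---|---|---|---|
| 190/115 | yes | yes | yes | yes |
| 210/100 | yes | no | **no** | yes |
| 170/125 | no | yes | **no** | yes |
| 170/100 | no | no | no | no |

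The two readings of the rule differ only in the second and third rows, that is, for people above exactly one limit. The printed rule sets no ceiling there: however high the systolic value, a diastolic value of 110 or less means that (e) is not met, and the same holds the other way round.

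**Does another passage close the gap?**

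- *Inclusion (d), Section 2.4.* A real gate that everyone must pass, but no blood-pressure limit is stated for it.
- *Exclusion (f), Section 2.4.* Also relies on the medical examination. It is worded for pathologies other than those already listed, so it is unclear whether it reaches blood pressure, which (e) already addresses. It states no limit.
- *Pre-test, Section 2.8 and Table 3.* Blood pressure is measured, but no eligibility or action limit is attached. By Section 2.5 and Table 1, this reading comes after randomisation.
- *Safety plan, Section 2.1.* Covers first aid, emergencies, referral and weather. It does not mention blood pressure.

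Exclusion (e) is therefore the only place with a numeric blood-pressure limit, and its outcome for anyone above one limit depends entirely on the connective.

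**The case against.** The strongest reply is that nobody enters on exclusion (e) alone. Inclusion (d) is a condition of entry in its own right, and a person with a very high single reading would have to be cleared at a medical examination that includes a stress EKG. Training is also individually adapted, the vigorous work is two four-minute bouts guided by the talk test and perceived exertion, and the autonomous walking is set at moderate intensity. Finally, 'and' may simply be loose drafting that lists two limits.

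Much of this stands. A reader might infer that people with severe hypertension will enter vigorous training. The documents do not support that: the examination may have stopped them, only the training group does the training, and nothing shows that anyone is above a single limit. The drafting explanation is plausible too, but it is a reason to correct the text. It does not show which rule was applied.

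A reader might also infer that the connective distorts blood pressure as an outcome. Suppose one participant has a systolic value of 200 mmHg in an arm of 26 whose other members average 135 mmHg. The arm mean rises by (200 − 135)/26 = 2.5 mmHg. That figure does not isolate the connective. A systolic value of 180 mmHg, with the diastolic value within its limit, is eligible under either reading and already raises the mean by (180 − 135)/26 = 1.7 mmHg. The connective adds only (200 − 180)/26 = 0.8 mmHg, on values that are assumed. With 1:1 randomisation and a repeated-measures analysis, one high baseline value is not in itself a bias. The case rests on the safety limit, not on the outcome analysis.

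**Conclusion.** The point holds as an internal contradiction in a stated safety limit. As written, exclusion (e) is not met by a person above only one of its two limits, its label suggests a wider group, and no other passage supplies a blood-pressure limit. This follows from the printed text and needs no assumption beyond reading 'and' literally.

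What does not follow is that anyone was wrongly enrolled. Entry of such a person is possible, not certain, because of the medical examination. The number affected is unknown and may be zero.

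Nor does it follow that 'or' is the right connective. The documents show a mismatch between label and definition. They do not show which of the two the sponsor intended, and that choice is clinical.

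The point is worth settling now rather than in the trial report because training has not begun. Until the first session, a check of readings can still change what happens to a participant.

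**What to change.** 1. The sponsor and its physician reconcile the label of exclusion (e) with its definition, and state whether exceeding both limits or either one was meant. The choice of rule and limits is theirs.
2. They state which reading was applied at screening. Since enrolment has closed, rewording alone does not change who was randomised.
3. Before the first training session, the screening readings on file and the planned pre-test readings are compared with the reconciled rule. Anyone who meets it is referred to the examining physician for a decision.
4. Every randomised participant stays in the intention-to-treat set, in line with Section 2.9, whatever the physician decides. The report gives the number identified, including if it is zero.

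The cost is a short clarification of the text and a check, in at least 52 people, of readings already taken or already scheduled. If the physician holds anyone back, the cost also includes that person's training exposure in an arm of about 26, which is a further reason to do the check before sessions start.
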